### Data analysis

Data will be collected for the duration of one year.

First, descriptive statistics of the characteristics of the intervention and the control group will be compared to check whether randomization resulted in similar groups.

The effectiveness of the intervention will be tested with ANOVA of the primary outcome measures. This gives us the opportunity to compare not only the intervention with mEUC (between groups effects), but also to do pre-posttest analysis for all participants (within subjects effects). Data will be analyzed in SPSS. Effect sizes will be expressed in Cohen’s *d* to make data comparable with earlier studies. Data will be analyzed both together and separately for the group 12–17 years old and 18–25 years old.

In e-health trials attrition is typically high and not all participants will use the intervention as intended. A participant will be excluded from analysis if he/she visited the intervention less than five times. His/her entry data (t = 0) will be used to describe baseline characteristics [56].

To interpret the findings, usage data, the WEQ, and the interviews held with the participants after finishing their participation will be analyzed alongside. Qualitative data will be analyzed with qualitative coding [57]. Interview data will be recorded and transcribed. Two researchers will study all transcripts independently, identify themes and establish the definite codes. Consensus will be reached in mutual discussion. Subsequently these outcomes will be formulated and interpreted in the supervising research group for final results. Quotes will be used to underline the results.

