**Figure 1 F1:**
[figure not shown]
**Flowchart randomization procedure, received care and data collection.** Abbreviations: mEUC = minimally enhanced usual care, UC = usual care.

The intervention group will receive immediate access to “Feel the ViBe” after registration. Considering ethical concerns of withholding an intervention with a possible positive effect on physical and mental health, the control group will be a waiting list condition receiving minimally Enhanced Usual Care (mEUC) for twelve weeks before getting access to the intervention. mEUC is in general defined as non-study care enhanced in minor ways to address methodological or ethical issues. For this RCT mEUC is defined as Usual Care and access to a restricted version of “Feel the ViBe” offering only access to the user profile, consent forms, digital testament, research information, questionnaires and the “ask the expert” function to ask questions in case of emergency. Questions asked by members of the control group will not be answered by the Community Manager, but by one of the members of the Research Team who is not actively involved in the intervention, being author [name]. If help is needed immediately, the participant will be referred to his/her GP (Figure 1).

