#### Primary outcome measure

•The Impact of Event Scale (IES) will be used to measure PTSD symptoms. The IES is a short set of 15 questions measuring the impact of events and the amount of distress associated with events. It comprises the subscales Intrusion (8 items, mean α = 0.86) and Avoidance (7 items, mean α = 0.82). The IES is measured at t = 0, t = 1, t = 2, t = 3 and t = 4 for both groups [44-46].

•The Depression and Anxiety subscales of the Symptom CheckList-90-R (SCL-90-R DEP and ANX) will be used to measure an improvement in symptoms of depression and anxiety. The SCL-90-R DEP and ANX subscales measure symptoms of depression and anxiety during the previous week on a five-point Likert scale. Both subscales showed good convergent and divergent validity, and high internal consistencies. The SCL-90-R is validated for participants of twelve years old and older. The depression subscale comprises 16 items (α = .90), the anxiety subscale comprises 10 items (α = .88). The SCL-90-R DEP and ANX subscales are measured at t = 0, t = 1, t = 2, t = 3 and t = 4 for both groups [47].

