### Randomization

Randomized trials with children and adolescents are controversial. The subject of our study enhances this even more. However to measure the effectiveness of an intervention, a randomized controlled trial is preferred above pre- post-test designs. Participants registering themselves online will be randomized to the intervention or the control group using the method of Minimization, as described by Taves (1974) [40,41]. Subcategories will be sex (male or female) and age (12–17 years old and 18–25 years old). This method minimizes the difference between the intervention and the control group. The allocation is carried out with help of a computer program by a research assistant.

Due to the nature of the study, participants cannot be blinded. Because of the nature of the overall study, containing both quantitative and qualitative parts, blinding of the investigators is difficult because the researchers need to know the group of the participant to be able to perform qualitative analysis and to follow each participant individually for the process evaluation. However questionnaires will be collected automatically during the trial in a SPSS file and delivered anonymized to the researchers.

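### The stated ANOVA of the primary outcomes does not adjust for the baseline score or the minimisation factors, and so gives up precision that the trial could have at almost no cost

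*Protocol article*

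**What the plan says.** All references are to the protocol article.

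- **Test.** Data analysis: "The effectiveness of the intervention will be tested with ANOVA of the primary outcome measures". The section adds that this allows a comparison between the groups "but also to do pre-posttest analysis for all participants (within subjects effects"), and that "Data will be analyzed in SPSS". It names no covariate.
- **Allocation.** Randomization, on the minimisation: "Subcategories will be sex (male or female) and age (12–17 years old and 18–25 years old").
- **Use of those factors.** Data analysis: "Data will be analyzed both together and separately for the group 12–17 years old and 18–25 years old". Sex is not mentioned in the analysis.
- **Waves.** Primary outcome measure: "The IES is measured at t = 0, t = 1, t = 2, t = 3 and t = 4 for both groups". The SCL-90-R depression and anxiety subscales follow the same schedule. Table 1 puts the follow-up waves at 6, 12, 18 and 24 weeks.
- **Length of the randomised contrast.** Intervention section, below Figure 1: controls receive "minimally Enhanced Usual Care (mEUC) for twelve weeks before getting access to the intervention". The randomised comparison therefore rests on t = 0, t = 1 and t = 2.
- **Attrition.** Data analysis: "In e-health trials attrition is typically high and not all participants will use the intervention as intended". No rate is given.

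**The concern.** A baseline score is available for each primary outcome, and allocation is balanced on two factors, but the stated test uses none of these as a covariate. If t = 0 enters as a wave, the arm-by-time term compares mean changes. If only follow-up scores are compared, baseline is not used. Both are less precise than regressing the follow-up score on baseline whenever r lies strictly between 0 and 1. Minimising on a prognostic factor and then omitting it from the model leaves its variance in the error term although the arms have been balanced on it, so the standard error is too large.

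What is at stake is power. The plan expects high attrition, removes participants with fewer than five visits and repeats the analysis in each age group, so the numbers actually analysed may be well below 50 per arm.

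**Working it through.** **Inputs from the article.** 95% confidence, 80% power, d from 0.7 (26 per group) to 2.0 (4 per group), 50 per group planned at t = 0.

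**Assumptions.** The article gives neither r nor a loss rate. I take r = 0.4 to 0.7 and, for illustration, 15% loss per wave.

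**1. The plan's own figure.** n per group = 2(z₁ + z₂)²/d², with z₁ for the significance level and z₂ = 0.842 for 80% power. With a one-sided 5% level (z₁ = 1.645) and d = 0.7, this is 2 × 2.487²/0.49 = 25.2, so 26; with d = 2.0 it is 3.1, so 4. Both stated figures are reproduced, for an unadjusted one-sided comparison. The two-sided number for d = 0.7 is 33 (normal) or 34 (t test). I use 34 per arm below because it is the two-sided size that gives about 80% unadjusted power.

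**2. Variance of the arm difference** (one baseline and one follow-up, equal SDs, relative to follow-up only = 1).

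- Follow-up only: 1
- Change score: 2(1 − r)
- Baseline-adjusted: 1 − r²
- Cut against change score: 1 − (1 − r²)/[2(1 − r)] = 1 − (1 + r)/2 = (1 − r)/2
- Cut against follow-up only: r²

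| r | Change score | Adjusted | Cut vs change | Cut vs follow-up only |
|---|---|---|---|---|
| 0.4 | 1.20 | 0.84 | 30% | 16% |
| 0.5 | 1.00 | 0.75 | 25% | 25% |
| 0.7 | 0.60 | 0.51 | 15% | 49% |

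**3. Two-sided 5% power** (noncentral t, effect d/√variance).

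| Setting | Follow-up only | Change score | Adjusted |
|---|---|---|---|
| 34 per arm, d = 0.7, r = 0.5 | 81% | 81% | 91% |
| 34 per arm, d = 0.7, r = 0.7 | 81% | 96% | 98% |
| 50 per arm, d = 0.7, r = 0.5 | 93% | 93% | 98% |
| 50 per arm, d = 0.5, r = 0.5 | 70% | 70% | 82% |
| 25 per arm (one age group, even split assumed), d = 0.7, r = 0.5 | 68% | 68% | 80% |

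**4. Minimisation factors.** In a simulation (50 per arm, minimisation on two binary factors, 6,000 replicates), the nominal 5% test without the factors had a type I error of 4.4%, 4.3% and 2.5% when they explained 5%, 10% and 20% of the outcome variance. With both factors in the model it was 5.0%, 5.3% and 4.6%. Omission errs on the conservative side.

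**5. Missed waves.** A standard repeated-measures ANOVA keeps only participants who have every wave entered. What that costs depends on two things the article does not state.

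- *Drop-out without return, 15% per wave.* 50 × 0.85² = 36.1 per arm reach t = 2, and the same people have t = 0 and t = 1. An ANOVA on t = 0 to t = 2 keeps all of them. Only if t = 3 and t = 4 also enter does the number fall to 50 × 0.85⁴ = 26.1.
- *Waves missed independently, 15% each.* An ANOVA on t = 0 to t = 2 keeps 50 × 0.85² = 36, while 50 × 0.85 = 42.5 have t = 2.

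**The case against.** The strongest reply is that little is lost. At 50 per arm and the smallest effect taken from the cited studies, unadjusted power is already about 93%. Baseline is not discarded, because a pre-post ANOVA uses it as a wave, and at r = 0.7 that ANOVA has 96% power at 34 per arm against 98% adjusted. Age is partly handled by the separate analyses. The article is also a condensed account, and covariates might be listed in a fuller plan.

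Most of this stands as a limit on size. It does not remove the point. The article does not leave the method open: it names ANOVA. Its Sample size section itself calls 0.5 a large effect, and at d = 0.5 the full sample has 70% power unadjusted and 82% adjusted at r = 0.5. Separate age-group analyses do nothing for the pooled test, and sex is absent throughout.

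Three stronger readings are tempting, and the documents do not support them.

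- *That the plan will drop everyone with a missed wave and fall to about 26 per arm.* The article does not mention repeated-measures ANOVA or listwise deletion and does not say which waves enter. The figure of 26 also needs t = 3 and t = 4, which come after controls gain access. Questionnaires are mandatory for access to other features, so skipping a wave and returning is less plausible than dropping out for good.
- *That drop-out probably depends on earlier scores, so the result is biased.* The article gives no drop-out pattern. This is a possibility, not a finding.
- *That omitting the minimisation factors invalidates the test.* It makes the test conservative.

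**Conclusion.** The point holds as one of efficiency. The stated ANOVA is less precise than a baseline-adjusted analysis for any r strictly between 0 and 1. Over the assumed range of 0.4 to 0.7, adjustment removes 30% to 15% of the variance against change scores and 16% to 49% against follow-up scores alone. With complete data and d = 0.7 the practical gain is small; it becomes material for smaller effects, within each age group and after attrition. Omitting sex and age group costs some further power if they are prognostic and does not inflate type I error. Loss through missed waves is conditional on how the ANOVA is run and which waves enter, and its size is unknown. The values of r, the loss rates and the even age split are my assumptions.

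**What to change.** For the randomised 12-week comparison, replace the ANOVA sentence with a baseline-adjusted analysis of each primary outcome:

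- a linear mixed model on t = 1 and t = 2 with arm, time, arm × time, that outcome's t = 0 score, sex and age group, using all available t = 1 and t = 2 data; or, more simply, ANCOVA at t = 2 with the same covariates;
- the arm difference at t = 2 with its 95% confidence interval as the reported result;
- Cohen's d obtained by dividing that difference by the baseline SD. Dividing by the residual SD would inflate d by 1/√(1 − r²), or 1/√0.75 = 1.15 at r = 0.5, and spoil the comparison with earlier studies that the plan wants.

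In the separate age-group analyses, drop the age-group term. The pre-post analysis of all participants can stay as supporting description.

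The cost is a change of wording and a little more analysis work. The t = 0 questionnaires are required before access, sex and age are already recorded for minimisation, and SPSS can fit either model.

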## Methods/design

### Trial design

This study is a randomized controlled trial using the method of minimization, as described by Taves (1974), to randomize the participants in two parallel groups with a 1:1 allocation ratio, being an intervention group, having access to “Feel the ViBe” + usual care (UC), and a control group, having access to minimally enhanced usual care (mEUC) [40,41]. Subcategories for the process of minimization will be sex (male or female) and age (12–17 years old and 18–25 years old). The study is conducted in the Netherlands. This trial is registered in The Netherlands National Trial Register (NTR) and assigned the trial ID NTR3692.

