### Sample size

For the calculation of de sample size of the RCT, we searched for studies investigating internet-based methods with the Impact of Event Scale (IES) as a primary outcome measurement [52-55]. We set the confidence interval to 95% and the power to 80%. We calculated the minimal sample sizes using the Cohen’s *d* effect sizes found in these studies. In general, an effect of 0.5 is considered to be a large effect. In the four selected studies, the effect size ranged from 0.7 (leading to 26 participants needed) to 2.0 (4 participants needed), with a mean of 11 and a median of 9 participants needed for each group. Considering the relatively high effect sizes found in these studies and because both the subject of the study and the age of the participants can lead to high drop-out, as seen before in a group of sexually abused adolescents, we aim to include 50 participants for each group at t = 0 [53].

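### The effectiveness ANOVA is not limited to the first twelve weeks, although controls get the intervention at t = 2, and the pre-post analysis of all participants does not start controls there

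*Protocol article*

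**What the plan says.** **Schedule.** For the first primary measure: "The IES is measured at t = 0, t = 1, t = 2, t = 3 and t = 4 for both groups". For the depression and anxiety subscales: "The SCL-90-R DEP and ANX subscales are measured at t = 0, t = 1, t = 2, t = 3 and t = 4 for both groups". Table 1 puts the occasions at first login and weeks 6, 12, 18 and 24.

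**Control condition.** The Intervention section says "the control group will be a waiting list condition receiving minimally Enhanced Usual Care (mEUC) for twelve weeks before getting access to the intervention". The Process evaluation section agrees: the web evaluation, due twelve weeks after access, falls at t = 2 in the intervention arm and t = 4 in controls. Controls therefore gain access at t = 2.

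**Analysis.** The Data analysis section tests effectiveness by ANOVA of the primary outcome measures. It gives as the benefit that one can "compare not only the intervention with mEUC (between groups effects), but also to do pre-posttest analysis for all participants (within subjects effects". It names no occasion and no model term, does not restrict the between-group comparison to the period when controls are on mEUC, and does not define pre and post separately by arm.

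**Related statements.** The Intervention section ties measurements to the twelve-week cycle. The Process evaluation section says the repeated primary measurements serve to find the optimal duration. The Randomization section prefers a randomised trial to pre-post designs.

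**The concern.** In a waiting-list design the randomised contrast ends when controls get access. Here only t = 1 and t = 2 compare the intervention with mEUC. An ANOVA that yields both between-group and within-subject effects reads most naturally as a repeated-measures model, and the only set of occasions the article gives is t = 0 to t = 4. An analyst could fit all five, report the group effect, and comply with the text. That effect would average in one occasion before treatment and two after crossover.

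The pre-post part has a different weakness. It stands under the effectiveness test and covers everyone. On the common time scale, the controls' first twelve weeks are time without the full intervention. Wherever it starts, the change is uncontrolled. Participants register themselves, and the Discussion describes them as actively searching for help, so natural recovery and regression to the mean are plausible.

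Two errors are at stake: missing a real 12-week effect, or claiming effectiveness from a change that has no comparator.

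**Working it through.** **1. The plan's own figure.** The Sample size section states "We set the confidence interval to 95% and the power to 80" per cent, and that "the effect size ranged from 0.7 (leading to 26 participants needed) to 2.0 (4 participants needed"). With n per group = 2((z_alpha + z_0.80)/d)²:
- one-sided 5%, d = 0.7: 2 × ((1.645 + 0.842)/0.7)² = 25.2, so 26; d = 2.0: 3.09, so 4;
- two-sided 5%, d = 0.7: 32.04, so 33 (34 with the noncentral t).

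The 26 reproduces as a one-sided comparison of two means at a single occasion. Sidedness is a separate matter. What matters here is that the sizing uses one contrast, not an average over occasions. Below I use two-sided 5% and the noncentral t.

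**2. What each occasion compares.**

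| Occasion | Week | Intervention arm | Control arm | mEUC comparator |
|---|---|---|---|---|
| t = 0 | 0 | not yet started | not yet started | no treatment effect possible |
| t = 1 | 6 | access | mEUC | yes |
| t = 2 | 12 | access | end of mEUC | yes |
| t = 3 | 18 | access | access | no |
| t = 4 | 24 | access | access | no |

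**3. Group main effect over five occasions.**

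From the article: d = 0.7 (the smallest effect it cites), "two parallel groups with a 1:1 allocation ratio", and "we aim to include 50 participants for each group at t = 0".

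Assumed, not in the article: differences of 0, 0.7, 0.7, 0.35 and 0 SD at t = 0 to t = 4; equal correlation r between occasions; no dropout.

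- Average difference = (0 + 0.7 + 0.7 + 0.35 + 0)/5 = 0.35 SD.
- SD of a five-occasion mean = sqrt((1 + 4r)/5).
- Noncentrality = standardised effect × sqrt(50/2) = standardised effect × 5, on 98 df.

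| r | SD of mean | Standardised effect | Power, 50 per arm |
|---|---|---|---|
| 0.5 | 0.775 | 0.452 | 61% |
| 0.6 | 0.825 | 0.424 | 56% |
| 0.7 | 0.872 | 0.401 | 51% |
| t = 2 alone | 1 | 0.700 | 93% |

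**4. Range.**
- At r = 0.3, power is 74%.
- If the difference vanishes at once after week 12, the average is (0.7 + 0.7)/5 = 0.28 SD and power is 43% to 36% for r = 0.5 to 0.7.
- If only 34 per arm were analysed, the profile in step 3 gives 45% to 37%, against 81% at t = 2. The article states no such number.

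**5. How much is due to crossover.** All at 50 per arm, r = 0.5 to 0.7.
- Without t = 0, the average is (0.7 + 0.7 + 0.35 + 0)/4 = 0.4375 SD and power is 78% to 69%. Had the 0.7 contrast lasted through t = 4, it would be 99% to 98%. Crossover alone therefore costs power.
- With t = 0 kept and a lasting contrast, the average is (4 × 0.7)/5 = 0.56 SD and power is 95% to 89%. Including baseline therefore also costs power.

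**6. Group-by-time interaction.** Noncentrality = (n/2) × Σ(difference − mean difference)²/(1 − r). Take d = 0.5, r = 0.5, 50 per arm and no difference after week 12:
- t = 0 to t = 2: 25 × 0.1667/0.5 = 8.33, power 72.9%;
- t = 0 to t = 4: 25 × 0.30/0.5 = 15, power 88.7%.

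Power rises, but partly because the curves converge once controls gain access. A significant result over five occasions does not show a difference at week 12.

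**7. Pre-post analysis.** For intervention participants, t = 0 to t = 2 is twelve weeks of access. For controls the same interval is mEUC, and their twelve weeks of access run from t = 2 to t = 4. A common interval of t = 0 to t = 2 would count 50 of the 100 planned participants without the full intervention.

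**The case against.** The strongest reply is that the article never says the between-group test uses all five occasions. It names the contrast as intervention against mEUC, and mEUC lasts twelve weeks by definition. The link of measurements to the twelve-week cycle points the same way, and the later measurements have their own stated purpose. The choice of ANOVA term and occasion is detail that a condensed article may leave to a fuller document. The dilution also needs one particular term, a main effect averaged over five occasions; with an interaction there is no loss in the scenario examined. As to pre-post, pre and post are not defined by arm, the web evaluation is timed by exposure in each arm, and the within-subject analysis is offered in addition to the randomised comparison.

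Much of this stands. A reader might infer that the plan does pool t = 3 and t = 4 into the treatment effect, or does count the controls' waiting weeks as treated time. The text supports neither as a statement of fact. A reader might also take 37-45% as the trial's power, but that needs an assumed 34 per arm as well as the five-occasion main effect.

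What does not stand is that only detail is missing. The mEUC wording and the twelve-week link point towards t = 2 without fixing it. The article does state an analysis, and it puts a pre-post analysis of all participants under the effectiveness test, with no separate start for controls and no ranking below the randomised comparison. That sits badly with the waiting-list design and with the article's own preference for randomised evidence.

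**Conclusion.** The point holds in a limited form. As written, the effectiveness analysis permits, but does not prescribe, a between-group comparison that includes two occasions without an mEUC comparator, and a pre-post analysis that includes the controls' waiting period.

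The possible cost is material: power of about 51-61% rather than about 93% at 50 per arm. This is conditional on a five-occasion group main effect, the assumed effect profile, r between 0.5 and 0.7, and no dropout. It is smaller at lower correlation, larger if the difference disappears immediately after week 12, and partly due to averaging in baseline. A comparison at t = 2 avoids it. An interaction test need not lose power, but does not answer the 12-week question.

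The pre-post part rests on no assumed figures: a within-subject change has no comparator, whichever interval is used.

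**What to change.** In the Data analysis section:

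1. State that the primary effectiveness test is the between-arm difference at t = 2 (week 12), with t = 1 supportive.
2. Use t = 3 and t = 4 descriptively only: maintenance in the intervention arm, and response after access in the control arm.
3. Start any pre-post analysis of controls at t = 2.
4. Label all within-subject results as uncontrolled and not as evidence of effectiveness.

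This changes analysis wording only. It needs no new data, no extra participants and no change to the measurement schedule. It should be fixed before outcome data are seen, so that the occasion and model term cannot be chosen on the results.

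### Separate effectiveness analyses in ages 12–17 and 18–25, with no stated comparison of effects between ages and no size set for either, can easily be significant in one age group only when the true effect is the same in both

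*Protocol article*

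**What the plan says.** All references are to the protocol article.

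- **Data analysis.** "The effectiveness of the intervention will be tested with ANOVA of the primary outcome measures". The same paragraph then adds: "Data will be analyzed both together and separately for the group 12–17 years old and 18–25 years old". No arm-by-age term, exploratory label or rule for reading discordant age results is given.
- **Sample size.** "We set the confidence interval to 95% and the power to 80"%. In the four source studies "the effect size ranged from 0.7 (leading to 26 participants needed) to 2.0 (4 participants needed"). Allowing for the drop-out it expects to be high, the article concludes: "we aim to include 50 participants for each group at t = 0". Here "group" means trial arm; no number or power is given for either age group.
- **Trial design and Randomization.** Allocation is to "two parallel groups with a 1:1 allocation ratio" by minimization: "Subcategories will be sex (male or female) and age (12–17 years old and 18–25 years old"). This balances the arms within each age group but does not fix how many participants fall in each.
- **Primary outcome measure.** Three scores are named: the IES and the depression and anxiety subscales of the SCL-90-R.

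**The concern.** The question of interest about age is whether the intervention works differently in minors and young adults. A significant result in one stratum beside a non-significant result in the other does not answer it, because the two p-values can fall on either side of 5% by chance when the effects are equal. That is most likely when each stratum has middling power, which is what halving a sample of 50 per arm produces over part of the effect range that the article discusses.

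At stake is a spurious statement that only one age group benefits, in a trial where age is built into the allocation and age-specific results will look planned. In addition, three tests per primary scale instead of one open more routes to a false-positive result.

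**Working it through.** **Inputs from the protocol article:** 50 per arm; 1:1 allocation; 80% power; 95% confidence; d from 0.7 to 2.0 in the source studies; d = 0.5, of which it says "In general, an effect of 0.5 is considered to be a large effect"; three primary scores.

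**Assumptions (not in the article):** even age split, so 25 per arm per age group, with 70:30 as a sensitivity case; no loss, or about one third lost, leaving 17 per arm per age group; two-sided 5% tests; correlation between scales of 0.7, range 0.3 to 0.9. Each comparison is treated as a two-group test at one time point, where ANOVA and the t-test coincide.

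**Step 1. The plan's own figures.** n per arm = 2(z_α + z_β)²/d².
- One-sided 5%: 2(1.645 + 0.842)² = 12.37. At d = 0.7, 12.37/0.49 = 25.2, so 26. At d = 2.0, 12.37/4 = 3.1, so 4. Both match the article.
- Two-sided 5%: 2(1.960 + 0.842)² = 15.70. At d = 0.7, 15.70/0.49 = 32.04, so 33 (34 by the exact t calculation).

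The stated 26 is thus reproduced only one-sided. That is a separate matter; the steps below use the usual two-sided test.

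**Step 2. Power within one age group.** Noncentral t with 2n − 2 degrees of freedom and noncentrality d√(n/2). For d = 0.7 and n = 25 this is 0.7 × 3.536 = 2.475 on 48 df, giving p = 67.9%. For n = 17 it is 2.041 on 32 df, giving p = 50.8%.

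**Step 3. Exactly one age group significant.** The strata contain different participants, so with equal power the chance is 2p(1 − p). At d = 0.7 and n = 25: 2 × 0.679 × 0.321 = 43.6%.

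| True d in both ages | Power, 25 per arm | Exactly one, 25 per arm | Power, 17 per arm | Exactly one, 17 per arm |
|---|---|---|---|---|
| 0.5 | 41.0% | 48.4% | 29.3% | 41.4% |
| 0.7 | 67.9% | 43.6% | 50.8% | 50.0% |
| 1.0 | 93.4% | 12.4% | 80.7% | 31.2% |
| 1.2 | 98.6% | 2.8% | 92.4% | 14.1% |

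With no true effect it is 2 × 0.05 × 0.95 = 9.5% per scale. With a 70:30 age split (35 and 15 per arm, no loss) the chance is 52%, 53%, 26% and 11% at the four values of d. An interaction test at the 5% level would wrongly signal an age difference in 5% of such trials.

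**Step 4. False positives with no true effect.** Simulation with normal test statistics, independent age strata of equal size, and the pooled statistic equal to the sum of the two stratum statistics divided by √2:

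| Correlation between scales | Three scales, overall only | Three scales, overall and both ages |
|---|---|---|
| 0.3 | 14% | 29% |
| 0.7 | 11% | 24% |
| 0.9 | 8% | 18% |

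At 0.7 the age strata therefore add about 13 points (23.7% − 10.9%); the other 11 come from having three primary scales.

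**Step 5. What an interaction test can detect.** With 25 per arm per age group, the standard error of the difference in d is √(4/25) = 0.40. The difference detectable with 80% power is (1.960 + 0.842) × 0.40 = 1.12. Power for a difference of 0.5 is 24%. With 17 per arm the detectable difference is 2.802 × √(4/17) = 1.36.

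**The case against.** The strongest case against the point has four parts.

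- **Silence is not a decision.** A reader might infer that the trial has chosen to omit an interaction test, or that it will claim an age difference from discordant results. The article supports neither. It is silent on an interaction test, which a full protocol or analysis plan may contain, and it states no hypothesis about age. This stands, so the point rests only on what is affirmatively planned: separate effectiveness analyses in strata for which no size is set.
- **The strata are legitimate.** They are named in advance, define the study population and are minimization factors, and the pooled analysis is planned too. This also stands. Pre-specification guards against picking subgroups after the fact, but it neither supplies power nor turns two p-values into a test of difference.
- **The size depends on the effect.** The cited effects run up to 2.0, and the median requirement of 9 per group corresponds to d of about 1.2 on the one-sided basis of Step 1. With no loss the discordant pattern is then rare. This stands and limits the point: the chance is near one half for d of 0.5 to 0.7, but not across the whole cited range.
- **The 24% is not all due to age.** A reader might attribute the whole figure to the age analyses. Nearly half is present before any age split. It also counts significant results in either direction; in favour of the intervention alone it is about 12%, against 5% for the overall tests.

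The interaction test's low power is a fair further criticism of the remedy, and explains why the age results need an exploratory label as well.

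**Conclusion.** The point holds in limited form. The article plans effectiveness analyses by age that are neither sized nor able, as stated, to show whether effects differ. If the true effect is equal in both ages, a result significant in one age group only is close to an even chance at d = 0.5 to 0.7 (41% to 50% over the two sample sizes shown). The chance is 12% to 31% at d = 1.0 and 3% to 14% at d = 1.2. With no true effect, the age strata roughly double the chance of at least one significant primary result, from about 11% to 24% at correlation 0.7.

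These figures rest on an even age split, assumed loss, assumed correlation and two-sided 5% tests, none of which the article gives. The pooled comparison is not invalidated. The article does not say that it will draw an age-specific conclusion; the point is that its stated analysis would not support one.

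**What to change.** Replace the separate age analyses with one model fitted in all participants, containing arm, age group and an arm-by-age-group term. Report the effect in each age group with its 95% confidence interval from that model and label these results exploratory. State that the claim of effectiveness rests on the overall comparison only.

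The cost is a change of wording, with no extra participants or data. What is given up is any age-specific claim of effectiveness. Because the interaction test reaches 80% power only for a difference in d of about 1.1 even with no loss, the text should also say that a non-significant interaction is not proof of equal effects.
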